## Background

Suboptimal nutrition during pregnancy may compromise maternal health, birth outcomes, and offspring development [1, 2]. Undernourishment in utero can stress the developing fetus and adversely reprogram its evolving phenotype [3]. Growth-restricted fetuses are thereafter predisposed to several perinatal health risks [4] including intrauterine growth retardation (IUGR), preterm delivery [5], low birth weight (LBW), immunocompromised status, childhood stunting, and neurocognitive deficits in addition to fetal, maternal, and infant mortality [6–8]. Hence, maternal undernutrition poses a significant global health burden [9], accounting for 7% morbidity [10] plus 70% neonatal [11] and 20% maternal [10] mortality rates worldwide. This situation is even more dismal for resource-constrained and food-insecure countries like Pakistan, where 18% of married women of reproductive age are nutrient-deficient, and thus 44% of children have stunted growth [12].

Maternal undernutrition is, in fact, a significant determinant of LBW in developing countries [13]. An indicator to measure LBW is small-for-gestational-age (SGA), defined as birth weight below the 10th percentile of optimal weight for a given gestational age and sex of a population subset [14]. Of the 23.3 million SGA births globally [15], around 20% are attributable to maternal undernutrition during pregnancy [16]. To address this, the World Health Organization Antenatal Care (WHO-ANC) guidelines recommend the use of fortified balanced energy protein (BEP) supplements during pregnancy to reduce the risk of stillbirth and SGA birth [17]. Following this recommendation, compositional guidance for a ready-to-use supplementary food (RUSF) for pregnant women was developed by the Bill and Melinda Gates Foundation (BMGF) in 2016 [18].

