### Anthropometry

The teams will be trained to perform anthropometric measurements for each mother-infant dyad using the INTERGROWTH-21st standards by a master trainer who will also conduct monthly refreshers. The measurements will include maternal height, mid-upper arm circumference (MUAC), and weight as well as infant length, weight, MUAC, and head circumference. SECA infant weighing scale model 334 will be used for infantile weight measurement whereas the SECA adult weighing scale model 874 will be used to assess the maternal weight. MUAC tapes from UNICEF will be imported. The SECA scale models 417 and 213 will be used to measure the maternal height and infantile length respectively. The team members recording anthropometric measurements will be blinded to the allocated arms of participants. Data will be entered digitally in the system which will automatically calculate the average value. The allowable difference between the two study measurements according to the standard procedure is ± 0.5 cm for maternal MUAC, ± 0.2 kg for maternal weight, ± 0.5 cm for maternal height, ± 20 g for infant weight, and ± 0.4 cm for infant length, infant MUAC, and infant head circumference.

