### Secondary outcomes

The other outcomes of interest will be birth length (cm), head circumference (cm), and MUAC (cm) of the newborn assessed in less than 72 h of birth. For extended follow-ups on days 3, 6, 21, 27, 42, 59, 89, 114, 143, 179, 269, and 359 from 0 to 11 months after birth, anthropometry of the mother-infant dyad will be assessed. Weight velocity (g/day), length velocity (cm/month), length-for-age *z*-score (LAZ), weight-for-age *z*-score (WAZ), and weight-for-length *z*-score (WLZ) will thereafter be calculated. Weight velocity is defined as the incremental change in weight (in grams) per day from birth to 11 months of age. Similarly, length velocity is defined as the progressive change in length (in centimeters) per month measured from birth to 11 months of infantile age. Moreover, the mean differences in the specific *z*-score indicators (LAZ, WAZ, and WLZ) measured at birth and 11 months of age will be assessed. Because anthropometric data for each mother-infant dyad is available on different periodic days as per their follow-up schedule, the aforementioned outcomes assessed according to each follow-up’s duration. Furthermore, the anthropometric measurements of the mother will also be assessed on a monthly basis during pregnancy, i.e., height (cm) (only at enrollment), weight (kg), and MUAC (cm), and body mass index (BMI). The mean change in each of these indicators for different arms will be assessed during pregnancy and in extended postnatal follow-ups.

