### Statistical analysis

All analyses will be done using Stata software version 16. Descriptive analysis of each group will be conducted, and percentages or continuous data with SD will be reported. The baseline characteristics will be assessed by arm. The primary approach will be intention-to-treat (ITT) analysis to compare primary and secondary growth outcomes. Mean differences will be assessed using one-way ANOVA, with the model adjusted for baseline characteristics including maternal age, BMI, gestational age, gravidity, MUAC, and newborn age at birth assessment. Key assumptions are that outcome data will be repeatedly measured, normally distributed, and following the superiority principle. For covariate analysis, both the unadjusted and stepwise-adjusted models will be run. Point estimates less than 10% will be reported as unadjusted despite of the model employed. Potential sub-group analyses for primary and secondary outcomes will be based on infantile gender and maternal data at enrolment, i.e., MUAC < 21.0 cm or ≥ 21.0 cm, age < 30 years or ≥ 30 years, gravidity < 3 or ≥ 3, and BMI < 18.5 kg/m^2^ or ≥ 18.5 kg/m^2^.

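### Infant sex and maternal height are not among the named covariates of the adjusted birth-weight model; fixing both in advance would gain a little precision at almost no cost

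*Protocol article*

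**What the plan says.** The Statistical analysis section plans a comparison of means from a model adjusted for a list of baseline covariates, opened by the word *including*: "maternal age, BMI, gestational age, gravidity, MUAC, and newborn age at birth assessment". It then adds: "For covariate analysis, both the unadjusted and stepwise-adjusted models will be run". It does not say which of these models is primary, and a 10% rule returns some estimates to their unadjusted form.

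Infant sex appears in that section only as a subgroup factor: "Potential sub-group analyses for primary and secondary outcomes will be based on infantile gender and maternal data at enrolment". The enrolment data meant are MUAC, age, gravidity and BMI.

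Elsewhere, the Background describes small-for-gestational-age as "birth weight below the 10th percentile of optimal weight for a given gestational age and sex of a population subset". The Anthropometry section states: "The measurements will include maternal height, mid-upper arm circumference (MUAC), and weight". Secondary outcomes shows that height is taken once, at enrolment: "height (cm) (only at enrollment), weight (kg), and MUAC (cm), and body mass index (BMI".

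**The concern.** The named set looks uneven in two ways.

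- **Sex.** Five subgroup factors are planned, and four of them (MUAC, age, gravidity, BMI) are also named covariates. Sex is the exception. The article's own definition of small-for-gestational-age pairs gestational age with sex; the first is named for the model and the second is not.
- **Height.** The set holds two overlapping measures of maternal thinness, BMI and MUAC, but no separate term for stature. BMI is weight divided by height squared, so it does not carry a linear effect of height on birth weight.

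Variation in birth weight that these two variables could explain would stay in the residual, and the standard error of each arm-versus-control difference would be slightly wider than the planned data allow. The same applies to birth length, head circumference and newborn MUAC.

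**Working it through.** **1. The plan's own figure.** The Sample size section gives a 100 g difference, 80% power, alpha 0.017 per comparison and 370 women per arm. It gives no standard deviation, so 370 cannot be reproduced forwards. Solving n = 2·SD²·(z_α + z_0.80)²/100² for SD:

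- one-sided 0.017: SD = 100·√(370/2)/(2.120 + 0.842) = 459 g
- two-sided 0.017: SD = 100·√(370/2)/(2.387 + 0.842) = 421 g

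The article calls the test one-tailed, so 459 g is used below, with 421 g as a check.

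**2. Share of variance (assumptions; the documents give none).**

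- Sex, with equal numbers of boys and girls: share = (d/2)²/SD². For d = 50 g, 25²/459² = 0.3%. For d = 100 g, 50²/459² = 1.2%. For d = 150 g, 75²/459² = 2.7%.
- Height: share = (slope × SD of height)²/SD². For 5 g/cm and 5.5 cm, 27.5²/459² = 0.4%. For 15 g/cm and 6.5 cm, 97.5²/459² = 4.5%.
- Together, taking sex as unrelated to maternal height: 0.7% to 7.2%, rounded to 1 to 7%. This treats the implied SD as the residual SD before the two variables are added. If BMI and MUAC already absorb part of the height effect, the true gain is nearer the low end.

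**3. Effect on precision and power at 370 per arm.** The residual SD becomes SD·√(1 − R²). Power is Φ[(z_α + 0.842)/√(1 − R²) − z_α].

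| Extra R² | SE of a difference (SD 459 g) | Power, one-sided 0.017 | Power, two-sided 0.017 |
|---|---|---|---|
| 0 | 33.8 g | 80.0% | 80.0% |
| 1% | 33.6 g | 80.4% | 80.5% |
| 3% | 33.3 g | 81.3% | 81.4% |
| 5% | 32.9 g | 82.1% | 82.3% |
| 7% | 32.6 g | 82.9% | 83.2% |

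Worked line for 7%, one-sided: 2.962/√0.93 = 3.071; 3.071 − 2.120 = 0.951; Φ(0.951) = 82.9%.

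**4. The same gain in women.** 370/(1 − R²) − 370 gives 370/0.99 − 370 ≈ 4 per arm at 1% and 370/0.93 − 370 ≈ 28 per arm at 7%. For scale, the dropout allowance is 471 − 370 = 101 per arm.

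**5. Is adjustment for sex safe?** Women are enrolled after 8 weeks of gestation, so sex is settled before allocation and treatment cannot change it. The plan already accepts a newborn-level covariate, age at the birth assessment.

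**The case against.** The strongest reply is that nothing here is wrong. The list is introduced as illustrative, the closed list normally belongs in the statistical analysis plan, and the choice of a seventh and eighth covariate is discretionary. Much of this stands. A reader might infer that the plan excludes sex and height; its wording does not support that. The open list does, however, sit beside stepwise adjustment, so whether either variable enters could be settled during the analysis. That is a reason to name them in advance.

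A reader might also infer a biased treatment effect or an underpowered trial. Neither follows. Randomisation makes the unadjusted contrast unbiased, and the sample-size text claims no variance reduction from covariates.

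Nor does the article show that both variables are recorded for everyone. Height is in the measurement set. Sex is not named among the case report form contents, and its collection is inferred from the subgroup plan. That inference is reasonable for a weighed newborn but not for every randomised pregnancy, since miscarriages and stillbirths are expected.

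Finally, if the unadjusted estimate is the one reported, naming two more covariates gains nothing. That limit stands in full.

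**Conclusion.** The point holds as a minor, nearly free improvement. The named covariates omit infant sex, which the article itself treats as a determinant of expected birth weight, and maternal height, which is measured at enrolment. The gain is about 0.4 to 3 percentage points of power, or about 4 to 28 evaluable women per arm. It rests on an assumed extra 1 to 7% of variance explained, on the SD implied by 370 per arm, and on the adjusted estimate being the one reported. That height predicts birth weight is itself an assumption; only sex has support in the document. No conclusion of the trial depends on this change.

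**What to change.** Prespecify infant sex and maternal height at enrolment as fixed covariates, outside any stepwise selection, in the adjusted model for birth weight, birth length, head circumference and newborn MUAC. The same sentence should say that the adjusted estimate is the one reported; otherwise the gain is not realised. Confirm that the birth assessment form records sex for every newborn weighed.

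The cost is one sentence in the analysis plan and two model degrees of freedom. Height needs no new measurement, and sex needs none if that check confirms it is recorded. The change should be made before the allocation code is revealed; the article plans database lock for June 2024.

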### Sample size

The sample size is calculated via permutation and subsequent adjustment for three comparisons between arms, i.e., intervention arms with control. Improved perinatal outcomes are hypothesized with the supplement of BEP alone or co-administration of BEP supplement with azithromycin as well as with nicotinamide and choline. Thus, the sample size estimated per arm is based on 1-tailed hypothesis testing of birth weight as the primary outcome, a significance level of 2.5% to account for multiple comparisons, and initial assumption of dropout proportion of 21% of study participants assumed in the trial. For birth weight (the primary outcome), it is assumed that the mean difference will be at least 100 g [30]. In order to achieve a test power of 80% and maintain family-wise error rate (FWER) of 0.05; Bonferroni method for three comparisons, alpha of 0.017, and an estimated sample size of 370 pregnant women per arm was attained. A 21% dropout rate was thereafter considered on account of miscarriages, stillbirths, early neonatal deaths, losses to follow-ups, and missed birth assessments due to varying on-field challenges owing to the pandemic. Hence, the sample size was thereafter adjusted to 471 pregnant women in each arm making up a total of 1884 pregnant women for this trial.

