### Primary outcome

The primary outcome of interest will be the birth weight (g) of the newborn assessed within 72 h of birth.

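### A 10% reporting rule and an undefined stepwise step let the observed data choose between adjusted and unadjusted estimates, so no single primary estimate of the birth-weight effect is fixed

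*Protocol article*

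**What the plan says.** All of this stands in the Statistical analysis section of the protocol article. On scope: "The primary approach will be intention-to-treat (ITT) analysis to compare primary and secondary growth outcomes". On the model: "Mean differences will be assessed using one-way ANOVA, with the model adjusted for baseline characteristics including maternal age, BMI, gestational age, gravidity, MUAC", followed by the newborn's age when measured. The word *including* leaves the list open. Next: "For covariate analysis, both the unadjusted and stepwise-adjusted models will be run". Then the reporting rule: "Point estimates less than 10% will be reported as unadjusted despite of the model employed".

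Nothing exempts the primary outcome, which the Primary outcome section defines in grams: "The primary outcome of interest will be the birth weight (g) of the newborn assessed within 72 h of birth". The article does not say what the 10% is a percentage of, what *stepwise* means, or which of the unadjusted, listed-covariate and stepwise estimates is the primary one.

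**The concern.** This is a stated rule, so an unseen analysis plan does not excuse it; a plan that followed the article would inherit it. The sentence can be read in three ways:

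- **Literal.** A point estimate below 10%. The treatment effect on birth weight is a difference in grams, so this has no meaning.
- **Change in estimate.** Report the unadjusted result if adjustment shifts the estimate by less than 10%. This is the most natural reading, but it is an inference. It is a tool for judging confounding in observational data. Under randomisation, covariates are adjusted for to gain precision, and little movement in the estimate is expected. The rule then discards the smaller standard error for no valid reason.
- **Small effect.** Report the unadjusted result if the effect itself is below 10% of something. The observed effect then selects the model.

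The first reading cannot be carried out. Under the other two, the observed data select the reported estimate, and the selection may differ from outcome to outcome. At stake are a primary result that is not uniquely determined in advance and some precision from covariates that the trial collects anyway.

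**Working it through.** **Inputs from the article (Sample size section).** 370 women per arm before dropout, 80% power, alpha 0.017, "1-tailed hypothesis testing of birth weight as the primary outcome", and for the effect "it is assumed that the mean difference will be at least 100 g". No standard deviation (SD) is given.

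**Assumed.** The change-in-estimate reading; R-squared (R²), the share of birth-weight variance that the covariates explain, from 0.05 to 0.3; and an SD back-solved from the article's own sample size.

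**Step 1: the SD behind 370 per arm.** The 370 cannot be reproduced without an SD, but it implies one: SD = 100 × √(370/2) / (z for alpha + z for power).

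- One-sided 0.017: 1360.1 / (2.120 + 0.842) = 459 g.
- Two-sided 0.017: 1360.1 / (2.387 + 0.842) = 421 g.

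The article says one-tailed, so 458 g (the value for alpha 0.05/3) is used below.

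**Step 2: what adjustment gains.** The unadjusted standard error is 458 × √(2/370) = 33.7 g. The adjusted one is 33.7 × √(1 − R²). Power is Φ(100/SE − 2.120). Unadjusted: 100/33.67 − 2.120 = 0.850, which gives 80%.

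**Step 3: how often the rule reports the unadjusted estimate.** The adjusted and unadjusted estimates differ by a random amount with SD 33.7 × √R². With a 100 g effect the 10% band is about ±10 g. The chance of reporting the unadjusted result is therefore about 2Φ(10 / (33.7 × √R²)) − 1.

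| R² | Adjusted SE (g) | Power, always adjusted | SD of the shift (g) | Chance that unadjusted is reported |
|---|---|---|---|---|
| 0.05 | 32.8 | 82% | 7.5 | 82% |
| 0.1 | 31.9 | 84% | 10.7 | 65% |
| 0.2 | 30.1 | 88% | 15.1 | 49% |
| 0.3 | 28.2 | 92% | 18.4 | 41% |

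**Step 4: simulation.** One comparison with control, 370 per arm, SD 458 g, one-sided alpha 0.017, one composite covariate, 20,000 replicates per setting. Here the band is 10% of the observed unadjusted estimate.

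| R² | Unadjusted reported | Power: always unadjusted / rule / always adjusted | Type I error under the rule |
|---|---|---|---|
| 0.1 | 64% | 80 / 83 / 84% | 1.5% |
| 0.2 | 49% | 80 / 87 / 88% | 1.3% |
| 0.3 | 41% | 80 / 90 / 92% | 1.2% |

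A large-sample check at R² 0.05 (normal estimates with the standard errors above) gave 78% reported unadjusted, power 81% under the rule against 82% always adjusted, and type I error 1.6%.

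**Step 5: sensitivity to sidedness and SD.** With a two-sided critical value of 2.394, SD 420 g and five covariates, the unadjusted result is reported in 66%, 52% and 46% of trials at R² 0.1, 0.2 and 0.3. Power under the rule is 82%, 86% and 90%, against 84%, 89% and 93% with fixed adjustment. The picture is the same.

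**The case against.** **The loss is small.** It is 1 to 3 points, and power under the rule never falls below the 80% the trial was sized for. This stands, and it rules out any claim that the rule leaves the trial underpowered.

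**Type I error.** A reader might infer that having two models per comparison inflates the error rate. The rule followed as written does not: simulated error was 1.2% to 1.6% against 1.7%. A rate of 2.2% to 2.6% at R² 0.1 to 0.3 appears only if success may be claimed from whichever model is more favourable, and the article does not propose that.

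**Stepwise.** A reader might take this to mean selecting covariates by significance. It can equally mean entering them in sequence. No stepwise selection was simulated, so no figure here speaks to it. The term still needs a definition, and on either meaning no single model is fixed.

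**The adjusted ANOVA comes first.** It could be the primary model, with the later sentences, which concern covariate analysis, being supplementary. That reading is possible. But the closing words of the 10% sentence apply it whatever model was used, and the list in the ANOVA sentence is itself open. The text is ambiguous at best.

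**Blinding.** The Blinding section keeps the final analyst and the investigators blind until the coded results have been reviewed. This limits choosing a model because it favours one arm. It does not say which model is reported.

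**Conclusion.** The concern holds and should be fixed. It rests mainly on the text: a data-dependent reporting rule covers the primary outcome, its wording cannot be applied uniquely, and nothing else in the article names the primary estimate. The secondary harm is lost precision. The unadjusted estimate would be reported in roughly 40% to 80% of trials, at a cost of about 1 to 3 points of power against always adjusting. Those figures depend on the change-in-estimate reading, on R² of 0.05 to 0.3 and on a back-solved SD, none of which the article states. The wording problem does not depend on them. The documents do not support a finding of inflated type I error or of inadequate power.

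**What to change.** Delete the 10% sentence and the stepwise step. Before unblinding, name one primary model for birth weight: an ANCOVA with trial arm, from which the three contrasts with control are taken, and a closed list of the covariates already named. These are maternal age, BMI, MUAC, gravidity and gestational age, all at enrolment. The article does not say when gestational age is taken; fixing it at enrolment keeps the adjustment to pre-randomisation information. The newborn's age at measurement arises after randomisation although it is listed among baseline characteristics. Keep it only as a measurement-timing covariate, with the reason stated.

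Always report this model as primary. Report the unadjusted difference once, as a sensitivity analysis, whatever its value.

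The cost is a few sentences of text. No new data or extra participants are needed. The Trial status section puts database lock in June 2024, with recruitment still open when the article was written, so at that stage the change could be made before lock.

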### Participants and public involvement

The investigators have extensive experience working with the community and their representatives/elders. During the protocol development phase, the team discussed and received feedback on the research question and trial design from the community representatives. Furthermore, community perspectives about the trial procedures, especially the frequency and duration of follow-up and biospecimen collection procedure, were also considered. Additionally, during the pilot phase, the aim was not only to test the consent form and questionnaires but also to understand the community response to different questions and how sensitive information regarding the antenatal and postnatal periods can be collected in a receptive and profound manner.

### Ancillary care

VPT will pay for ancillary care in case the participants incur any harm owing to trial participation or have health issues not monetarily covered by the national healthcare program.

### Confidentiality

During the trial, the data files containing personal identifying information will be stored in a password-secured server. Only the members in the top hierarchy of the research team, i.e., principal investigator and project coordinators, will have access to those files. Moreover, biological samples collected from the field site will be de-identified to respect the privacy of study participants.

### Dissemination plan

Processes will be developed to facilitate collaborative data-sharing for scientific purposes. De-identified data with analytical/statistical codes will be made available to the public domain 2 years after the publication of the principal manuscripts. However, investigator support will be needed for which the approval of the proposal and counter-signatures of the data access agreement are a requisite. The data will be uploaded on a password-secured cloud server at all times.

